### Interim analyses

At the end of the first phase of the test (V3), an interim analysis of the data from the previous stage will be conducted by the biostatistician of the data monitoring committee, who will primarily analyse the size of the estimated effect in advance and the incidence of adverse events. If there is a lack of treatment effect or the incidence of adverse events is high, early termination of the trial will be considered. These results will be reported back to the trial sponsor, and he or she will decide whether to terminate the experiment or not.

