
### Sample size

Based on the assumption that a reduction of 25% in VAS scores would be of clinical significance, enrolment of 44 patients in each group is required at the 5% significance level (two-tailed), with a power of 90% to detect differences between the two groups [19]. Considering a 10% possible dropout rate, at least 49 people need to be enrolled in each group.

In this study, we will recruit 60 people for a placebo-controlled, double-blind, crossover trial. After crossover, both the placebo and experimental groups will each be increased to 60 people.

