### Concealment mechanism

Random sequences will be successively assigned to the subjects according to the enrolment order.

Odd-numbered subjects will be entered into group 1, and even-numbered subjects will be entered into group 2. Three copies of the generated distribution sequence table will be distributed among the designer, pharmacist, and statistician. Each copy will be sealed in an opaque envelope and kept under lock.

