## Assignment of interventions: blinding

### Who will be blinded

The placebo used in the study looks and smells indistinguishable from mite bait and will be labelled either A or B. The identity of tag A or tag B will be known only to the pharmacists and unknown to the subjects and researchers.

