### Frequency and auditing of trial conduct

The Project Management Group will meet once a month to review the trial. The Trial Steering Group and the independent Data Monitoring and Ethics Committee will meet to review conduct throughout the trial period 12 months after the trial is approved.

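### The V3 interim analysis passes first-period effect results, not just a committee recommendation, to the sponsor, who may stop for lack of effect on an unpaired comparison of about 30 v 30

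*Protocol article*

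**What the plan says.** The Interim analyses section fixes the timing: "At the end of the first phase of the test (V3), an interim analysis of the data from the previous stage will be conducted". The analyst is the biostatistician of the data monitoring committee, who "will primarily analyse the size of the estimated effect in advance and the incidence of adverse events". The stopping grounds follow: "If there is a lack of treatment effect or the incidence of adverse events is high, early termination of the trial will be considered". The last sentence names the recipient and the decision-maker: "These results will be reported back to the trial sponsor, and he or she will decide whether to terminate the experiment or not".

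Three other sections bear on this:
- Who will be blinded: "The identity of tag A or tag B will be known only to the pharmacists and unknown to the subjects and researchers".
- Procedure for unblinding: the sealed sequence is opened, and data are classified as test or control, once the trial has ended. No interim step is described.
- Composition of the data monitoring committee: the committee is independent of the sponsor and its role is to advise.

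**The concern.** Two features of the interim look cause difficulty.

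**Flow of results.** An independent committee normally protects a blinded trial by seeing the comparative data and passing on only its advice. Here the results themselves go to the sponsor. Group 1 receives package A then B, and group 2 receives B then A. The first-period contrast between groups is therefore a contrast of A with B, and its sign points to the active package for the rest of the trial. The primary outcome is a subjective symptom score, so knowledge of interim results is undesirable while scores are still being collected.

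**Strength of the evidence.** The design relies on each child receiving both packages. At V3 each child has received only one, so the within-child contrast does not yet exist. A judgement that there is no effect would rest on a smaller, noisier comparison than the one the trial was sized for, and an effective product could be stopped.

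**Working it through.** **1. Inputs.** From Sample size: two-sided 5%, 90% power, 44 per group, a 25% VAS reduction as the target, and 10% dropout. Also from Sample size: "In this study, we will recruit 60 people for a placebo-controlled, double-blind, crossover trial". From Concealment mechanism: "Odd-numbered subjects will be entered into group 1, and even-numbered subjects will be entered into group 2". Period 1 is therefore about 30 v 30. This split is derived, not printed. Applying the 10% dropout to it gives 30 × 0.9 = 27 per group, an assumption for V3.

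**2. The plan's own figures.** 44 / 0.9 = 48.9, which rounds up to the stated 49. The 44 cannot be reproduced forwards because no SD or control mean is given. Solved backwards:

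d = (1.960 + 1.282) × √(2/44) = 0.691 SD (0.699 with the noncentral t).

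For a 25% reduction this implies an SD of 0.25 / 0.691, about 36% of the control mean.

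**3. Power of the V3 comparison at that effect.** Power = Φ(d / √(2/n) − 1.960).
- n = 30: 0.691 / 0.258 = 2.677; Φ(0.717) = 76.3% (t: 75.9%).
- n = 27: 0.691 / 0.272 = 2.539; Φ(0.579) = 71.9% (t: 71.2%).

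**4. Chance of apparent lack of effect when the true effect equals the target.** The article does not define the term, so the plausible readings are set out (normal approximation):

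| Reading | Formula | 30 v 30 | 27 v 27 |
|---|---|---|---|
| Estimate at or below zero | Φ(−d/√(2/n)) | 0.4% | 0.6% |
| Estimate below half the target | Φ(−½d/√(2/n)) | 9% | 10% |
| Not significant at two-sided 5% | 1 − power | 24% | 28% |
| Estimate below the target | Φ(0) | 50% | 50% |

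**5. Sensitivity to the unstated SD.** Power at 30 v 30 is 97%, 90%, 68% and 49% for an SD of 0.25, 0.30, 0.40 and 0.50 of the control mean.

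**6. Information at V3 relative to the completed crossover.** With N children, the period-1 contrast has variance 4/N and the within-child contrast 2(1 − ρ)/N, in SD² units. The ratio of information is (1 − ρ)/2. For an assumed within-child correlation ρ of 0, 0.3, 0.5 or 0.7, this is 0.50, 0.35, 0.25 or 0.15. Even at ρ = 0, a paired analysis of all 60 has Φ(0.691 × √(60/2) − 1.960) = Φ(1.825), about 97% power. Whatever the stopping threshold, and for any non-negative correlation, V3 offers at most half the final information.

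**The case against.** A sponsor who decides after committee advice is ordinary practice. Termination is only to be considered, so the rule is already discretionary. A numerical threshold may sit in an analysis plan or committee charter, so its absence from the article is no fault. Parents complete the questionnaires, submitted answers cannot be changed, and the staff member who checks them does not know the grouping, so no route from sponsor knowledge to biased scores is documented. All of this stands, and it limits the size of the point. It does not answer the sentence that sends the results themselves to the sponsor, or the use of the first-period contrast to judge efficacy.

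Three stronger readings are tempting, but the documents do not support them:
- *The trial is no longer blind to the sponsor.* The text discloses aggregate effect and adverse-event results, not individual allocations, and the A/B code stays with the pharmacists. A signed result points to the active package but does not open the code. Whether the odd/even rule would then reveal each child's sequence depends on which number it refers to.
- *A specific loss of overall power.* This would need a written rule of stopping on non-significance, a within-child correlation and no second-period data at the time of stopping. The article gives neither of the first two. With staggered enrolment, some children would already have crossed over by the last V3.
- *The committee meets too late to act at V3.* The auditing section says the oversight groups "will meet to review conduct throughout the trial period 12 months after the trial is approved". That sentence concerns conduct and its timing is unclear, and the interim is assigned to the committee's biostatistician rather than to that meeting. It cannot carry a date argument.

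**Conclusion.** The point holds as a should-fix. The interim text makes the sponsor no longer blind to comparative interim results, and it must be reconciled with the sections on blinding, end-of-trial unblinding and the independent committee. These do not say how a V3 treatment effect is to be obtained, or how it can reach the sponsor with blinding preserved.

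The efficacy ground is applied to an unpaired comparison with about 76% power (71-72% after dropout), against the 90% planned with 44 per group. The risk of wrongly judging the planned effect absent runs from about 0.4% to 50%, depending on how lack of effect is read; 24-28% applies only if it means non-significance. These figures assume an equal split of 60 and the standardised effect implied by 44 per group. The unstated SD could move power at V3 well in either direction.

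**What to change.** - State that comparative V3 results stay within the independent committee and that the sponsor receives only a recommendation to continue or stop.
- Either limit the V3 look to safety or base any non-binding futility assessment on the final within-child crossover analysis, for example low conditional power under the planned 25% effect, rather than on the period-1 comparison alone. Conditional power needs a within-child correlation; the assumed value and a range should be stated.
- Align the interim, blinding, unblinding and committee sections, saying who prepares the V3 comparison and under what access to the A/B code.

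The cost is wording. The small downside is that a truly ineffective product is less likely to be stopped early.

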### Methods for additional analyses

When evaluating factors affecting rhinitis and asthma control, multiple linear regression or logistic regression will be used.

### Analysis methods to account for protocol non-adherence and statistical methods to be applied for missing data

For subjects that are randomized to the intervention but do not adhere to the intervention, if they completed the first phase of the trial before the crossover, their data will be retained, and the shortest distance filling method or multiple filling method will be used to assess the missing data; otherwise, the observed samples will be deleted.

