### Criteria for discontinuing or modifying allocated interventions

If the research physician feels that it is not in the child’s best interest to continue participating in the study (e.g. if there is an allergic reaction to the mite bait or placebo used), he/she may decide whether to withdraw the child from the study at any time. If a subject’s parents fail to complete the questionnaire after 3 reminders or fail to cooperate with the indoor sample collections, the subject will be considered poorly compliant and will be excluded from the study.

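### Exclusion for poor cooperation, deletion of incomplete first-phase data and an optional single-filling method let behaviour after randomisation shape the VAS result

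*Protocol article*

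**What the plan says.** Two sections of the protocol article decide whose data count.

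*Criteria for discontinuing or modifying allocated interventions* deals with parents who "fail to complete the questionnaire after 3 reminders or fail to cooperate with the indoor sample collections". In that case "the subject will be considered poorly compliant and will be excluded from the study". No exception is made for how far the child has got. The same section separately lets the research physician withdraw a child in the child's interest; that provision is not at issue here.

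*Analysis methods to account for protocol non-adherence and statistical methods to be applied for missing data* opens "For subjects that are randomized to the intervention but do not adhere to the intervention". For these children, "if they completed the first phase of the trial before the crossover, their data will be retained". Either nearest-distance or multiple filling is then "used to assess the missing data; otherwise, the observed samples will be deleted". The last clause covers those who did not complete phase 1.

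The primary outcome is the VAS for rhinitis symptoms. The mattress sample serves a secondary outcome, the dust mite antigen level. *Interim analyses* plans a look at the first-phase data at V3, which may lead to early termination. The *Discussion* itself expects loss to follow-up and falling compliance.

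**The concern.** Both rules select children on what happens after randomisation. A family that will not allow a mattress sample can lose the child's place in the VAS comparison as well, although the VAS may still be obtainable. A non-adherent child who stops during phase 1 has real VAS measurements thrown away.

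If stopping is linked to symptoms, and is more frequent under one package than the other, the children left in the two sequences are no longer comparable. The documents contain a possible route: the adverse-event section lists eye irritation among possible effects of emamectin, and the VAS scores itchy, teary and red eyes. A child who did badly on the bait in phase 1 and stopped would have those scores deleted. Nothing shows that this will happen, but the deletion rule leaves the result exposed to it. It would bear most directly on the V3 interim analysis, which has only first-phase data, and on the between-group tests named in *Statistical methods*, where a child's first period counts by itself.

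Filling is a separate matter. On its natural reading, shortest-distance filling is single nearest-neighbour imputation: one borrowed value is entered and then analysed as if it had been measured. That adds apparent sample size without adding information.

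**Working it through.** **1. The two rules side by side.** Take a child who finishes phase 1 and whose parents then refuse the V4 sample. The discontinuation section excludes the child. If the child is counted as non-adherent, the missing-data section keeps the data and fills the gaps. If refusing a sample is not non-adherence to the intervention, the missing-data section is silent. The text does not say which reading applies.

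**2. The plan's own loss figure.** *Sample size* states "enrolment of 44 patients in each group is required at the 5% significance level (two-tailed), with a power of 90" per cent, then allows 10% dropout. 44 / 0.90 = 48.9, rounded up to 49, so the stated 49 reproduces. The 44 cannot be checked, because no SD or control mean is given. The 10% is the only loss rate in the document and anchors step 3.

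**3. Precision under single filling (simulation).** Sixty children, 30 per sequence; score SD 1; no treatment effect. Assumed: within-child correlation 0.3, 0.5 or 0.7, and 10%, 20% or 30% of second periods missing at random. A missing second period takes the value of the child in the same sequence with the nearest first-period score. The analysis compares (period 1 − period 2) between sequences by a t test, with 4000 runs per setting. The simulation error of a true 0.05 is √(0.05 × 0.95 / 4000) = 0.003.

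| Second periods missing | Reported SE / true SE, filled | Type I error, filled |
|---|---|---|
| 10% | 0.90–0.94 | 0.065–0.075 |
| 20% | 0.84–0.86 | 0.091–0.093 |
| 30% | 0.76–0.80 | 0.111–0.139 |

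With only the children who have both periods, the SE ratio was 0.97–1.00 and type I error 0.048–0.053 throughout. The SE is therefore 1 − 0.94 = 6% to 1 − 0.90 = 10% too small at 10% missing, and 14–16% too small at 20%.

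**4. Bias from selective loss (simulation).** Same set-up, correlation 0.5, no true effect, 3000 runs (simulation error of type I error 0.004). Children with high (bad) first-period scores are preferentially removed; the loss patterns are assumed.

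| Lost, bait-first v placebo-first | Bias (SD units) | Type I error |
|---|---|---|
| 10% v 10% | −0.004 | 0.050 |
| 20% v 20% | 0.000 | 0.050 |
| 5% v 15% | 0.019 | 0.054 |
| 10% v 30% | 0.055 | 0.064 |
| 0% v 20% | 0.058 | 0.072 |

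A positive value makes the bait look worse. With no true effect the set-up is symmetrical, so heavier loss in the bait-first sequence reverses the sign and favours the bait. In step 3, with loss at random, neither dropping incomplete children nor filling shifted the estimate by more than 0.004 SD.

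**The case against.** Several stronger readings are tempting, and the documents do not carry them.

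- *One missed questionnaire or sample removes a child.* The text requires three failed reminders, or failure to cooperate with sampling. A single missed sample is not stated as a trigger.
- *The rules bias the result.* Step 4 shows bias only when loss depends on outcome and is unequal between sequences. A child without a second period also adds nothing to a purely within-child contrast, so deletion there mainly wastes first-period data.
- *The plan overstates precision.* Only the single-filling option does. Multiple filling is named as the alternative and, properly pooled, is meant to carry the uncertainty; it was not simulated.
- *The exclusion rule uses up the dropout allowance.* Seven questionnaires and four samples make 11 occasions, and at an assumed 1% or 2% failure each, 1 − 0.99^11 = 10.5% or 1 − 0.98^11 = 19.9% of children would go. The rates have no source, and the samples fall at questionnaire visits. Counting seven visits gives 1 − 0.99^7 = 6.8% or 1 − 0.98^7 = 13.2%. The plan recruits 60, each supplying both arms, against 44 needed, so (60 − 44) / 60 = 27% can be lost on its own reckoning.
- *The two sections flatly contradict each other.* One may govern who continues and the other how collected data are analysed; the consent section, which asks about use of data after withdrawal, fits that reading. What stands is that the text does not say so.

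It can also be said that choosing an imputation method is detail for the analysis plan. That would excuse silence. Here the article states a deletion rule, states an exclusion rule and expressly admits single filling. It does not say which values are filled; step 3 assumes whole second periods.

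**Conclusion.** The point holds and should be fixed. The article states rules under which cooperation after randomisation can decide which of 60 children enter the primary comparison, deletes the observed data of non-adherent children who do not complete phase 1, and leaves the choice between single and multiple filling open.

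The overstatement of precision is conditional on single filling being chosen and its values being treated as observed. At the protocol's own 10% loss it is modest; it grows quickly with more missing data. These figures rest on the assumed correlations and on loss at random.

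Bias is a possibility whose size the documents cannot fix. Under the assumed unequal losses it was about 0.02 to 0.06 SD, in a direction set by which sequence loses more. The lowest of the corresponding type I errors, 0.054, is within simulation error of 0.05.

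**What to change.** 1. State that failing to return a questionnaire or to allow a house sample does not remove a child from the analysis, and go on collecting the VAS where the family agrees.
2. Remove the rule that deletes observed data when phase 1 is incomplete.
3. Analyse all randomised children by assigned sequence, with all observed VAS data, in a mixed model with treatment, period and sequence and a random effect for child. The article names no such model, so it has to be added. It uses incomplete children without filling and is valid if loss depends only on observed data. Retaining first-period scores is what lets it allow for loss related to them.
4. Drop single nearest-distance filling. Prespecify multiple imputation, pooled in the usual way, as a sensitivity analysis.
5. Present per-protocol results as supportive only.
6. Reconcile the two sections: say that one governs continuation and the other analysis, and what happens to a child who finishes phase 1 and then stops cooperating. Say also which data enter the V3 interim analysis.

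The physician's withdrawal provision stays as written. The cost is wording and modest extra follow-up of incomplete cases; no additional children are needed.

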### Access to the full protocol, participant-level data, and statistical codes

The datasets analysed during the current study are available from the corresponding author on reasonable request.

## Oversight and monitoring

### Composition of the coordinating centre and Trial Steering Committee

In this trial, the sponsor hires staff member [name] to publish recruitment information through WeChat and collect basic information of the participants. The information will be shared with [name] to select qualified research subjects. After confirming eligibility, [name] will contact the child’s guardian and acquire written informed consent. Throughout the trial, two professional staff members will be responsible for collecting indoor samples and replacing mite bait or placebo. At the same time, one staff member will be responsible for regularly providing electronic questionnaires to the enrolled subjects to follow-up the symptoms of the children and summarize the adverse events during the trial. [name] will evaluate the reliability of each uploaded follow-up questionnaire. During the trial, the Trial Steering Committee, composed of [name] and [name], will review the progress and safety of the trial.

### Composition of the data monitoring committee

The data monitoring committee (DMC) includes a biostatistician, a respiratory professional physician, and a patient advocate to advise the sponsors and principal investigators regarding the continuing safety of study patients and the scientific merit of the study. The DMC is independent of the sponsor and competing interests. The DMC is responsible for monitoring the recruitment of participants, compliance with the protocol and data quality, serious adverse events, and other safety questions.

### Adverse event reporting and harms

During the trial, we will collect and record the occurrence of adverse events, describe the date of onset and date of resolution, evaluate event severity, investigate potential causal relationships with the intervention or with other suspect drugs, and assess the potential effect of the event on the final outcome, which will be reported to the DMC and ethics committee.

The mite bait will be placed under the mattress and will not be in direct contact with the child. However, the acute oral, transdermal, and inhalation toxicity of the 0.1% emamectin in the mite bait is considered to be slight, and thus, the mite bait needs to be secure. Some adverse events that may occur with emamectin include skin and eye irritation, nausea, vomiting, headache, dizziness, fatigue, chest tightness, excessive sweating, salivation, blurred vision, convulsions, and tachycardia or bradycardia.

Severity should be defined according to the following criteria:
Mild: Awareness of signs or symptoms, but easily toleratedModerate: Sufficient discomfort to cause interference with normal daily activitiesSevere: Inability to perform normal daily activitiesLife threatening: Immediate risk of death from the reaction as it occurred

All adverse events will be tracked until the incident is resolved or the study is completed.

